### Strategies to improve adherence to interventions {11c}

At each assessment visit, patients will return all empty blister packs and unused trial drug to check for compliance; they will then be given a sealed package containing the next 10 or 20 days’ treatment with trial drug or placebo. Investigators will ensure accountability for all drugs delivered/returned by patients using a drug accountability form.

### Relevant concomitant care permitted or prohibited during the trial {11d}

Permitted concomitant medications include analgesics, stool softeners, fecal emollients, and any treatments taken for unrelated conditions that will not interfere with the study drug.

Drugs that may interfere with the evaluation of the study drug or alter the evaluation of efficacy parameters are not permitted as concomitant therapy. These include (but are not limited to) oral anticoagulation therapy (e.g., warfarin, acenocoumarol), novel oral anticoagulants (e.g., rivaroxaban, apixaban, and dabigatran), and anti-platelet agents (e.g., double-anti-aggregation or acetylsalicylic acid > 160 mg/day and ticlopidine).

### Provisions for post-trial care {30}

After the end of the trial (last visit of the last patient enrolled), any new serious adverse drug reactions or any new information about previously recorded AEs will be reported by the Investigators to the Sponsor. All AEs detected during the trial will be followed up until resolved, judged to be stable or no further information on the event/final outcome is possible.

### Outcomes {12}

#### Primary outcomes

The primary objective of the trial is to demonstrate the superiority of mesoglycan versus placebo in reducing symptoms of HD (i.e., the change in HDSS from baseline to day 40). The HDSS is a 5-item questionnaire that asks patients about HD symptoms experienced using a scale of 0 (never) to 4 (every day/always). Total score ranges from 0 to 20, with a higher score indicating more frequent and severe symptoms [29]. Symptoms of HD will be assessed using the HDSS at baseline (day 0; T0), day 10 (T1), day 20 (T2), and day 40 (T4).

#### Secondary outcomes

Secondary objectives of the trial are to assess (i) changes in HRQoL from baseline to day 40 using the Short Health Scale for Hemorrhoidal Disease (Short Health Scale_HD_); (ii) safety (AEs, physical assessments, vital signs and laboratory parameters); (iii) fecal continence (using the Vaizey score); (iv) bleeding (assessed via study-defined bleeding score); (v) the amount and type of analgesics taken (using frequency tables); and (vi) pain (measured using a visual analog scale [VAS]). The Short Health Scale_HD_ is composed of four questions on how hemorrhoids affect the patient’s daily life, with answers given on a 7-point Likert Scale, and the final total score ranges from 4 to 28 (a higher score indicates worse quality of life) [29]. The Vaizey score measures fecal incontinence, with a score of 0 indicating perfect continence and the maximum score of 24 indicating total incontinence [30]. Bleeding was assessed on a scale of 0–4, where 0 = no bleeding, 1 =  ≤ 1 episode per month, 2 =  ≤ 1 episode per week, 3 = 1–3 episode(s) per week, and 4 = 4 episodes per week. A VAS will be used to measure pain, with a score of 0 indicating no pain and a score of 10 indicating maximum pain.

Assessment of secondary outcomes will take place at baseline, day 10, day 20, and day 40, with the exception of fecal incontinence, which will be assessed only at baseline and day 40.

Patients will also be questioned on day 70 (via telephone) regarding AEs.

AEs occurring from signing of the informed consent form until 30 days after the last administration of study drug or placebo will be recorded and classified according to the latest version of the Medical Dictionary for Regulatory Activities. AEs will be summarized according to system organ class and primary preferred terms, and their severity and relationship to study treatment assessed by the Investigator.

Patient-reported outcomes were assessed via a daily diary, in which patients were encouraged to document the frequency of their main symptoms in order to facilitate clinical evaluation during visits.

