## Introduction

### Background and rationale {6a}

Hemorrhoidal disease (HD) is the most common proctological disease, with an estimated prevalence of 11–39%, peaking in individuals aged 45–65 years [1–3]. HD is associated with a substantial economic burden and can negatively affect health-related quality of life (HRQoL) [2, 4].

The most common presentation of HD is painless rectal bleeding occurring during or immediately after defecation [3, 5, 6]. Other symptoms, typically associated with prolapsed or large hemorrhoids, include rectal itching or swelling, a sensation of rectal fullness, fecal soiling, and pain [3, 5–7]. The Goligher classification system [8] is typically used to grade the severity of HD [3, 6]. This system is based on the presence and severity of prolapse, and ranges from Grade I (hemorrhoidal engorgement above the dentate line but no prolapse) to Grade IV (prolapsed hemorrhoids that cannot be reduced manually, possibly accompanied by inflammatory changes, mucosal atrophy, and ulceration). However, it is important to note that the Goligher classification system does not consider a wide range of symptoms, apart from bleeding in Grade I HD, special conditions such as pregnancy or inflammatory bowel disease, comorbidities or the presence of a single or circumferential prolapse, which may introduce bias and interobserver variability between physicians on assessing HD using the Goligher classification [9].

Effective treatments for Grade I–III internal hemorrhoids include diet and lifestyle modifications and medical treatments (e.g., topical glucocorticoids, vasoconstrictors, analgesics) and/or, in the event of failure, outpatient non-operative procedures such as rubber band ligation, sclerotherapy, and infrared coagulation [3, 5, 6, 10, 11]. In patients with thrombosed external hemorrhoids, topical vasodilators (e.g., nifedipine, glyceryl trinitrate) can relieve pain and reduce the size of the hemorrhoid [11]. If these treatments are ineffective, or in the event of high-grade and symptomatic hemorrhoids, surgical intervention is indicated [6, 10, 12]. Patients awaiting surgery can obtain relief through use of local or systemic anti-inflammatory agents [12].

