	**Visits**				
	**T0 (Baseline; Day 0)**	**T1 (Day 10 [± 2 days])**	**T2 (Day 20 [± 2 days])**	**T3 (Day 40 [± 2 days])**	**T4 (Day 70**^**a**^**)**
Written informed consent	X				
Eligibility screen	X				
Demographic data	X				
Objective examination and vital signs	X	X	X	X	
Pathological anamnesis	X				
Previous/concomitant treatments	X	X	X	X	
Pregnancy test	X				
Blood test^b^	X			X	
Proctological examination^c^	X	X	X	X	
Treatment group allocation (i.e., randomization)	X				
Assessment of symptoms (HDSS)	X	X	X	X	
Assessment of HRQoL (SHS-HD)	X	X	X	X	
Assessment of bleeding (Bleeding score)	X	X	X	X	
Assessment of faecal continence (Vaizey score)	X			X	
Assessment of pain (VAS score)	X	X	X	X	
Assessment of AEs		X	X	X	X
Study treatment adherence		X	X	X	
Drug dispensing	X	X	X		

^a^Telephone follow-up

^b^Includes complete blood count, PTT, PT, TT, functional antithrombin III, functional fibrinogen, creatinine, AST, ALT, and CRP

^c^Includes rectal exploration and anoscopy (if applicable)

*AEs*, adverse events; *ALT*, alanine aminotransferase; *AST*, aspartate amino transferase; *CRP*, C-reactive protein; *HDSS*, Hemorrhoidal Disease Symptom Score; *HRQoL*, health-related quality of life; *PT*, prothrombin time; *PTT*, partial thromboplastin time; *SHS-HD*, Short Health Scale for Hemorrhoidal Disease; *TT*, thrombin time; *VAS*, visual analog scale.

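### The study-defined bleeding score gives 1 episode per week two codes, and gives no code to rates above 4 or between 3 and 4 per week

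*Protocol article*

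**What the plan says.** The Secondary outcomes section lists "bleeding (assessed via study-defined bleeding score") as objective (iv) of six. The Short Health Scale and the Vaizey score each carry a literature reference. The bleeding score carries none, so the wording in the article is the only definition available to the reader.

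That wording is:

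- Range and code 0: "Bleeding was assessed on a scale of 0–4, where 0 = no bleeding".
- Code 1: at most "1 episode per month".
- Codes 2 and 3: code 2 is at most "1 episode per week, 3 = 1–3 episode(s) per week".
- Code 4: the sentence closes with "episode(s) per week, and 4 = 4 episodes per week".

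On timing, the same section states: "Assessment of secondary outcomes will take place at baseline, day 10, day 20, and day 40", with fecal incontinence as the only exception. Table 1 (Participant timeline) agrees: its row "Assessment of bleeding (Bleeding score") is marked at T0, T1, T2 and T3. Statistical methods {20a} has every endpoint analyzed at each timepoint, both as an absolute value and as a change from baseline. The article gives no rule for ties and no open-ended top level. It states no look-back period for this score.

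**The concern.** An ordinal score works only if every patient falls into exactly one level. Here a patient who bleeds once a week can properly be given 2 or 3, and nothing tells raters at the two centers which to choose. A patient who bleeds daily has no level at all. A rater must either round down to 4 or leave the item blank, and a blank would be missing precisely because the bleeding is heavy.

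Bleeding is not a marginal symptom in this disease. The Background says: "The most common presentation of HD is painless rectal bleeding occurring during or immediately after defecation". With 25 patients planned per arm, an avoidable one-point ambiguity on a five-level scale costs precision in an endpoint that the trial names as an objective.

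**Working it through.** The article states no figure that could be reproduced here. The check is to take a range of episode rates and see which codes each one satisfies.

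**Inputs.** The five code definitions come from Secondary outcomes. The visit days (0, 10, 20, 40) come from Secondary outcomes and Table 1. A month is taken as 30.4 days (an assumption), so 1 per month = 7 / 30.4 = 0.23 per week.

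**Two readings.** The literal reading applies each bound exactly as printed. The ordered reading is the charitable one: code 1 is more than 0 and up to 1 per month, and code 2 is more than 1 per month and up to 1 per week. The last column applies the levels proposed under the fix.

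| Episodes per week | Literal | Ordered | Proposed levels |
|---|---|---|---|
| 0 | 0, 1, 2 | 0 | 0 |
| 0.1 | 1, 2 | 1 | 1 |
| 0.23 (1 per month) | 1, 2 | 1 | 1 |
| 0.5 | 2 | 2 | 2 |
| 1 | 2, 3 | **2, 3** | 3 |
| 2 | 3 | 3 | 3 |
| 3 | 3 | 3 | 3 |
| 3.5 | none | **none** | 3 |
| 4 | 4 | 4 | 4 |
| 5 | none | **none** | 4 |
| 7 (daily) | none | **none** | 4 |

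The bold cells are faults that survive even the charitable reading: one tie, at exactly 1 per week, and two uncovered ranges, between 3 and 4 per week and above 4 per week. The overlap of codes 1 and 2 does not survive it.

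**The gap between 3 and 4.** This does not arise if whole episodes are counted in a single week. It arises when a count is averaged over a longer interval. With rate per week = 7 × episodes / days, 5 episodes in 10 days give 7 × 5 / 10 = 3.5, which has no code. Six episodes give 7 × 6 / 10 = 4.2, which is above 4 and also has no code.

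**Look-back (conditional, because the article states no window).**

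- If raters count only since the last visit, 1 episode in 10 days is 30.4 / 10 = 3.0 per month, and 1 in 20 days is 30.4 / 20 = 1.5 per month. Both exceed 1 per month, so on the ordered reading code 1 could not be reached after baseline.
- If raters look back one month, the day-10 score reaches 30.4 − 10 = 20.4 days before treatment and the day-20 score 30.4 − 20 = 10.4 days. The day-40 score lies wholly within treatment (40 − 30.4 = 9.6 days after the start).

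These lines show only what would follow under each assumption.

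**The case against.** The strongest reply is that raters would cope. On an ordered scale one takes the lowest code that applies, so 1 per month is code 1, and only exactly 1 per week stays ambiguous. A patient who bleeds more than four times a week would most likely be scored 4, which is also the value under the proposed wording. A sign for at least may have dropped out before the last 4 in a condensed article, and the full protocol and e-CRF are not shown. Patients and investigators are blinded, so how a tie is broken should not depend on treatment.

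Much of this stands. The overlap between codes 1 and 2 is not a real difficulty, and forcing heavy bleeders to 4 would usually do no harm. Nobody can say from the article how many patients will fall at 1 per week or above 4. The tie at 1 per week remains, however, and neither order nor common sense settles it. The signs for at most are intact in the same sentence, so the definition has to be taken as written. An open top level would in any case leave the tie, and the gap between 3 and 4, in place. Blinding guards against favoring an arm; it does not remove the noise.

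A reader might go further and infer that the monthly level cannot be measured at 10-day visits, or that early scores carry pre-treatment bleeding. The documents do not support this as an error. Each version presumes a look-back period that the article does not state, and a condensed article may leave that detail to the full protocol or the e-CRF.

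**Conclusion.** The point holds as a fault in a stated definition. As printed, exactly 1 episode per week has two codes, and rates above 4 per week, or averaged rates between 3 and 4, have none. This rests on the article's wording alone and survives the charitable reading.

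Severity is low to moderate. The score serves one secondary objective. The primary endpoint, its test and the sample size all rest on the HDSS and are untouched. A reader might infer that the bleeding endpoint as a whole cannot be scored consistently. That is too strong, because most rates have a single code on an ordered reading and the heaviest bleeders would probably be placed at 4. The loss of precision cannot be quantified, since the article gives no distribution of bleeding frequency.

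**What to change.** Redefine the levels so that each rate has exactly one:

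- 0 = no bleeding
- 1 = more than 0 and up to 1 episode per month
- 2 = more than 1 per month but less than 1 per week
- 3 = 1 to fewer than 4 per week
- 4 = 4 or more per week

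Level 3 must run up to just below 4. Keeping it at 1–3 and merely opening the top level would still leave 3.5 per week without a code.

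Enter these definitions in the e-CRF. Before unblinding, check scores already recorded against the diary or source records where these exist.

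If a look-back period is set, use the same one at baseline and at every later visit, and make it compatible with the levels. A 7- or 10-day window cannot keep a monthly level: 1 episode in 10 days is already about 3 per month, and 1 in 7 days is 1 per week, which is level 3.

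The cost is a small e-CRF edit and a blinded check of existing entries. The check may be incomplete, because patients were only encouraged to keep the diary and the article describes no diary before baseline.

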### Participant timeline {13}

The participant timeline is shown in Table 1.

**Table 1 Tab1:** Participant timeline

	**Visits**				
	**T0 (Baseline; Day 0)**	**T1 (Day 10 [± 2 days])**	**T2 (Day 20 [± 2 days])**	**T3 (Day 40 [± 2 days])**	**T4 (Day 70**^**a**^**)**
Written informed consent	X				
Eligibility screen	X				
Demographic data	X				
Objective examination and vital signs	X	X	X	X	
Pathological anamnesis	X				
Previous/concomitant treatments	X	X	X	X	
Pregnancy test	X				
Blood test^b^	X			X	
Proctological examination^c^	X	X	X	X	
Treatment group allocation (i.e., randomization)	X				
Assessment of symptoms (HDSS)	X	X	X	X	
Assessment of HRQoL (SHS-HD)	X	X	X	X	
Assessment of bleeding (Bleeding score)	X	X	X	X	
Assessment of faecal continence (Vaizey score)	X			X	
Assessment of pain (VAS score)	X	X	X	X	
Assessment of AEs		X	X	X	X
Study treatment adherence		X	X	X	
Drug dispensing	X	X	X		

^a^Telephone follow-up

^b^Includes complete blood count, PTT, PT, TT, functional antithrombin III, functional fibrinogen, creatinine, AST, ALT, and CRP

^c^Includes rectal exploration and anoscopy (if applicable)

*AEs*, adverse events; *ALT*, alanine aminotransferase; *AST*, aspartate amino transferase; *CRP*, C-reactive protein; *HDSS*, Hemorrhoidal Disease Symptom Score; *HRQoL*, health-related quality of life; *PT*, prothrombin time; *PTT*, partial thromboplastin time; *SHS-HD*, Short Health Scale for Hemorrhoidal Disease; *TT*, thrombin time; *VAS*, visual analog scale.

### Sample size {14}

The trial aims to enroll a total of 50 patients (25 patients in each treatment group). This sample size is based on an assumed between-group difference in HDSS score of 1.8 points with a standard deviation (SD) of 1.7 (based on results of previous studies [31, 32]), an alpha of 0.05, and a two-tailed *t*-test with 90% power to reject the null hypothesis (i.e., the averages of the two treatment groups are equal) and an expected drop-out rate of approximately 10%.

### Recruitment {15}

Patients will be recruited in hospital when they voluntarily come for a coloproctological examination, until the sample size (*n* = 50) is reached or until October 10, 2024, whichever comes first.

## Assignment of interventions: allocation

### Sequence generation {16a}

The randomization list will be generated by an independent statistician, with stratification according to HD severity (Grade I–III vs external thrombosed hemorrhoids).

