## Methods: participants, interventions, and outcomes

### Study setting {9}

The trial is being conducted at two tertiary referral centers in Italy – Azienda Ospedaliero Universitaria Consorziale Policlinico, Bari, and Clinica Santa Rita di Vercelli, Presidio di Policlinico di Monza, Monza.

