## Data collection and management

### Plans for assessment and collection of outcomes {18a}

The CRO, Clinical Trial Consulting, will create and manage the e-CRFs on behalf of the study Sponsor. The Sponsor will then provide this set-format e-CRF to investigators to record the required trial data at each visit (day 0–day 70), with internal controls to help ensure correct data entry. Trial data for each participant will be entered into the e-CRF by the Investigator and collated by the study centers. All safety data (AEs, physical examinations, vital sign measurements and laboratory assessments) will be recorded in patients’ medical records and in the e-CRF. Data cleaning analysis conducted by the Data Manager (an employee of CMV-Stat, Rome, Italy) will identify any inconsistencies to the Investigator for validation (i.e., modification or acceptance).

At the end of the trial, the database will be frozen by the Data Manager and the data sent to the biostatistics unit of CMV-Stat for statistical analysis. All methods used for statistical analyses of data will be listed in detail in the statistical analysis plan (SAP), which will be finalized in Version 1.0 of the SAP, prior to the database lock.

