## Statistical methods

### Statistical methods for primary and secondary outcomes {20a}

The statistical analysis of data from the trial will be conducted by a statistician from CMV-Stat on behalf of the Sponsor.

All the variables will be analyzed descriptively using means with SDs, medians with interquartile ranges (IQRs), minimum and maximum values, and 95% confidence intervals (where appropriate) for continuous variables, and numbers, percentages, and missing data for categorial variables.

For all trial endpoints, analyses will be performed on each timepoint in absolute terms and as changes from baseline. Efficacy endpoints will be analyzed according to the stratification factor of the presence of uncomplicated HD versus thrombosed hemorrhoids. Efficacy analysis will be applied in the intention-to-treat (ITT) and per protocol (PP) populations and safety/tolerability will be assessed in the safety population. The ITT population is defined as all patients who have taken ≥ 1 dose of study drug/placebo and who have ≥ 1 post-baseline assessment for the primary endpoint. The PP population is defined as all enrolled patients who have data from all observations, met all inclusion/exclusion criteria, not taken any unauthorized drug, and taken ≥ 80% of the study drug/placebo. The safety population is defined as all patients who have signed informed consent and have taken ≥ 1 dose of study drug/placebo.

For the primary endpoint (i.e., change in HDSS from baseline to day 40 in the ITT population), the *t*-test will be applied with a significance level of 5%. If assumptions of normality and homoscedasticity are unmet, a corresponding non-parametric test will be applied.

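### Two centres, but neither the stratification nor the stated primary test accounts for centre: a small, avoidable loss of precision if the centres differ, with no bias

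*Protocol article*

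**What the plan says.** - Protocol article, Study setting {9}: "The trial is being conducted at two tertiary referral centers in Italy", one in Bari and one in Monza.
- Sequence generation {16a}: the list is drawn up "with stratification according to HD severity (Grade I–III vs external thrombosed hemorrhoids". No other factor is named.
- Statistical methods {20a}: the primary endpoint, HDSS change from baseline to day 40 in the ITT population, is compared by t-test at the 5% level. The fallback reads: "If assumptions of normality and homoscedasticity are unmet, a corresponding non-parametric test will be applied".
- The same section adds: "Efficacy endpoints will be analyzed according to the stratification factor of the presence of uncomplicated HD versus thrombosed hemorrhoids". Hemorrhoid type is the only factor named for efficacy.
- Plans for assessment and collection of outcomes {18a}: "All methods used for statistical analyses of data will be listed in detail in the statistical analysis plan (SAP". That plan is to be final before database lock and is not available here.

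**The concern.** A two-sample t-test, or its usual rank counterpart, has no place for centre, and the list does not balance the arms within centre. If mean HDSS change differs between the hospitals, two things follow. The difference adds to the residual variance and widens the interval. A chance imbalance of the arms across centres also moves the estimate up or down at random. Some difference is conceivable, because background care is left open ("Permitted concomitant medications include analgesics, stool softeners, fecal emollients") and each hospital sees the patients who happen to attend it. At stake is precision in a trial of 50 patients. Centre is known for every patient, so any such loss could be avoided without new data.

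**Working it through.** **Inputs from the Sample size {14} section.** "an assumed between-group difference in HDSS score of 1.8 points", SD 1.7, two-sided alpha 0.05, 90% power, about 10% dropout, 25 per arm.

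**Inputs not in the documents (assumed).** Centre difference in HDSS change, c: 0 to 2.5 points. Share of patients at the larger centre, p: 50% or 70%.

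**1. The plan's own figure.** The exact t-test calculation gives 19.76, so 20 per arm; 20/0.9 = 22.2, so 23 per arm, or 46 in total. The plan has 50, so it errs on the safe side; that is a separate matter. With 10% dropout, 25 × 0.9 = 22.5, so 22 evaluable per arm is used below. Power there is 92.9%.

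**2. Unadjusted t-test, with 1.7 read as the within-centre SD.** Total SD = √(1.7² + p(1−p)c²), and SE = total SD × √(2/22). For c = 1.7 and p = 0.5, total SD = √(2.89 + 0.25 × 2.89) = 1.901 and SE = 0.573, against 1.7 × √(2/22) = 0.513 for c = 0.

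**3. Linear model with centre.** The residual SD stays at 1.7 whatever c is. Power is averaged over the chance split of the arms across centres, with 41 residual degrees of freedom, and comes to 92.3%.

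| Centre difference (points), p = 0.5 | Total SD | Power, unadjusted | Power, centre in model |
|---|---|---|---|
| 0 | 1.700 | 92.9% | 92.3% |
| 0.85 | 1.752 | 91.4% | 92.3% |
| 1.7 | 1.901 | 86.6% | 92.3% |
| 2.5 | 2.110 | 78.9% | 92.3% |

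Adjustment breaks even at about 0.55 points. Unadjusted power drops below 90% when the total SD reaches about 1.80, which is a centre difference of about 1.2 points (about 1.3 with a 70/30 split). With all 25 per arm evaluable, it is still 90.7% at 1.7 points.

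**4. If 1.7 is the total SD across centres.** Unadjusted power is 92.9% whatever c is. With c = 1.7 the within-centre SD would be √(2.89 − 0.25 × 2.89) = 1.47, and adjusted power about 97%.

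**5. Chance imbalance (hypergeometric).** Probability that the arms differ by 20 percentage points or more in centre share:

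| Patients | Equal centres | 70/30 |
|---|---|---|
| 44 | 13.1% | 18.5% |
| 46 | 23.8% | 10.8% |
| 50 | 25.8% | 21.7% |

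The range is thus about 10% to 26%; it is uneven because counts are whole numbers. A gap of 20 points with c = 1.7 moves the estimate by 0.2 × 1.7 = 0.34 points, or 0.34/1.8 = 19% of the planned effect, in either direction.

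**6. Type I error.** In simulation of the unadjusted t-test without centre stratification, it stays at 4.5% to 5.3% for centre differences from 0 to 2.5 points.

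**7. Cost when the centres do not differ.** The simulated SE goes from 0.515 to 0.521, a ratio of 1.012, so the interval is about 1% wider. Power falls by 92.9 − 92.3 = 0.6 points.

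**The case against.** The strongest reply is that the detailed methods are left to a SAP that is not shown, and an article's silence on a covariate does not prove that centre will be ignored. This stands in part: the SAP may already include centre. But the article does name the primary test, and that test cannot take a centre factor. The stratification factor is also already fixed.

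Three stronger readings are tempting, and the documents support none of them.

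- A reader might infer that the treatment comparison is biased or its error rate inflated. It is not. Chance imbalance is ordinary random error that the standard error already covers.
- A reader might infer that the two centres are known to differ. The Discussion's remark on more severe disease concerns both centres together, and the concomitant-medication rules are the same at both. Taking change from baseline also removes a pure difference in starting level, though not a difference in change.
- A reader might infer that the trial is underpowered. The loss arises only if 1.7 is a within-centre SD, which the sample size section does not say, and only beyond about 1.2 points does power fall below the planned 90%. A difference of 1.7 points would be 1.7/1.8 = 94% of the assumed treatment effect, which is large.

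It is also fair to say that not stratifying by centre is a defensible choice in a trial of this size.

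**Conclusion.** The point holds as a minor matter of efficiency. Centre is absent from the stratification and from the stated primary test, so any centre difference in HDSS change remains in the random error. With a within-centre SD of 1.7 and 22 per arm in equal centres, adjustment loses 0.6 points of power if there is no difference, gains about 1 point at 0.85 and gains nearly 6 points at 1.7. If 1.7 is the total SD, the plan loses nothing and adjustment only adds precision. The size of any real centre difference is unknown. The validity of the primary comparison is not in question, and the change is worth making only because it is cheap.

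**What to change.** Leave the running randomisation list unchanged. Before database lock, specify the day-40 HDSS comparison, and the other continuous efficacy comparisons, as a linear model with treatment, hemorrhoid-type stratum and centre (two levels) as fixed factors. Replace the unstratified non-parametric fallback with a stratified rank test such as van Elteren's, with strata formed from hemorrhoid type and centre. Show the treatment difference by centre descriptively only.

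This replaces the stated t-test rather than adding a term to it, so the change from the published method should be documented. It needs no new data. Centre uses one degree of freedom; if the centres do not differ, that costs under 1 point of power and about 1% in interval width. Crossing the two factors gives up to four strata in 44 to 50 patients, and some may be sparse, so the SAP should say how an empty or one-armed cell is handled in the rank test.
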